### Outcome measures

2.7

The outcomes of this study were designed to evaluate both the clinical efficacy and neurophysiological changes associated with acupuncture treatment in patients with chronic tinnitus. Considering the different characteristics of subjective symptom assessment and electrophysiological evaluation, clinical and neurophysiological outcomes will be analyzed separately.

The assessment schedule is summarized in Table 1. Patient-reported outcomes, including tinnitus severity and related functional impairment, will be assessed at baseline (T0), after completion of acupuncture treatment (T1), and at the 8-week (after the beginning of acupuncture treatment) follow-up visit (T2). Auditory brainstem response (ABR) measurements will be performed in both the healthy control group and the tinnitus patient group at baseline (T0) and after treatment completion (T1), as the primary purpose of the electrophysiological assessment is to evaluate changes in auditory pathway function during the course of treatment. ABR testing will not be conducted at the follow-up visit, as the primary purpose of the follow-up assessment is to evaluate the durability of subjective tinnitus improvement.

#### Primary outcomes

2.7.1

##### Primary clinical outcome

2.7.1.1

The primary clinical outcome will be the change in the Tinnitus Handicap Inventory (THI) score from baseline to post-treatment and follow-up.

The THI is a quick, simple, and psychometrically sound tool that assesses how tinnitus affects day-to-day functioning. The THI has 25 questions with three main subscales (affective, functional, and severity scores) and a total scale score of 0–100, with lower scores indicating less severe tinnitus-related handicap. It has been shown to be an accurate and significant indicator of self-reported tinnitus-related discomfort (38).

##### Primary neurophysiological outcome

2.7.1.2

The primary neurophysiological outcome will be the change in ABR wave V latency from baseline to post-treatment.

Previous studies have suggested that alterations in ABR latency parameters may represent objective neurophysiological changes associated with tinnitus-related auditory dysfunction. Wave V latency was chosen because it exhibits the highest test–retest reliability among ABR parameters and is the most clinically robust and widely reported metric in human auditory brainstem assessment. Although wave I amplitude is mechanistically important and is discussed in the introduction as a candidate biomarker of cochlear synaptopathy, its variability is substantially influenced by individual anatomical factors, making it less suitable as a primary endpoint for sample size estimation.

#### Secondary outcomes

2.7.2

##### Secondary clinical outcomes

2.7.2.1

1) Tinnitus effects questionnaire: One of the most used instruments for evaluating tinnitus is the Tinnitus Effects Questionnaire (TEQ). The six factors that comprise the composite score used to measure the severity of the tinnitus are the environment in which it occurs, its duration, its effect on sleep and work-study, its disruption of mood, and the patient’s overall assessment of the tinnitus’s severity. More severe tinnitus is indicated by higher scores. The scale is broken down into five grades: Grade I (1–6 points), Grade II (7–10 points), Grade III (11–14 points), Grade IV (15–18 points), and Grade V (19–21 points) (39). The TEQ will be used as a complementary tinnitus-specific questionnaire to evaluate tinnitus characteristics and symptom burden. Compared with THI, which primarily focuses on functional and emotional consequences, TEQ provides additional information regarding tinnitus perception and daily-life impact. Its shorter completion time and applicability in Chinese clinical populations make it suitable as a supplementary patient-reported outcome measure.2) Tinnitus loudness and annoyance visual analogue scales (VAS): Two 0–10 VAS scores will be collected to evaluate subjective tinnitus loudness and tinnitus-related annoyance. Higher scores indicate greater perceived loudness or distress. These simple and sensitive measures will provide additional information regarding short-term symptom changes that may not be fully captured by standardized questionnaires (40).

##### Secondary neurophysiological outcomes

2.7.2.2

Secondary neurophysiological outcomes will include additional ABR parameters, including: wave I amplitude and latency, wave III amplitude and latency, wave V amplitude, interpeak latencies (I–III, III–V, and I–V).

### Statistical analysis

2.8

Statistical analyses will be performed using SPSS version 27.0 (IBM Corp., Armonk, NY, USA). All statistical tests will be two-sided, with a significance level of *p* < 0.05. Baseline demographic and clinical characteristics will be summarized using descriptive statistics. Continuous variables will be presented as mean ± standard deviation (SD) or median (interquartile range, IQR), depending on data distribution, while categorical variables will be expressed as frequencies and percentages. Normality of continuous variables will be assessed using the Shapiro–Wilk test and visual inspection of Q–Q plots. For the control group, ABR measurements will be performed at two time points (T0 and T1, matching the interval of the patient group) to assess test–retest variability. This allows us to distinguish treatment-related changes from normal variability. For bilateral ABR measurements, the primary analysis will be conducted at the participant level by averaging measurements from both ears.

For baseline comparisons between tinnitus participants and healthy controls, paired-sample t-tests or Wilcoxon signed-rank tests will be used according to data distribution, because controls will be individually matched with tinnitus participants based on age and sex.

Longitudinal changes in ABR parameters will be analyzed using two-way mixed-design analysis of variance (ANOVA), with group (chronic tinnitus vs. healthy control) as a between-subject factor and time (baseline vs. post-treatment/retest assessment) as a within-subject factor. If significant between-group differences in audiometric profiles are detected at baseline or within each group, corresponding frequency-specific hearing thresholds will be included as covariates in the analyses. The primary parameter of interest will be the group × time interaction effect, which will determine whether changes in ABR parameters over time differ between tinnitus participants and healthy controls. If the interaction is significant, simple main effects will be examined with Bonferroni correction. Intraclass correlation coefficients (ICC, two-way random-effects model) will be calculated for each ABR parameter in healthy controls to assess test–retest reliability. Within-group changes between baseline and post-treatment/retest assessment will also be examined using paired-sample *t*-tests or Wilcoxon signed-rank tests when appropriate.

Clinical outcomes, including THI, TEQ, and tinnitus-related VAS scores, will be evaluated only in tinnitus participants using one-way repeated-measures ANOVA across baseline, post-treatment, and 8-week follow-up. When assumptions of normality or sphericity are violated, appropriate non-parametric tests or Greenhouse–Geisser corrections will be applied. Associations between changes in ABR parameters and changes in subjective tinnitus severity will be explored using Spearman rank correlation analysis. For secondary analyses involving multiple ABR parameters, false discovery rate (FDR) correction using the Benjamini-Hochberg procedure will be applied to control for multiple comparisons.

Missing data will be assessed and reported. Linear mixed-effects models or multiple imputation methods will be considered for sensitivity analyses if substantial missing longitudinal data occur.

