In addition, although the following measures will not reduce the placebo effect, we will take further steps to ensure the overall scientific rigor and interpretability of the study results. Baseline characteristics of all participants will be compared to verify the comparability between the tinnitus and healthy control groups. During recruitment, participants will be provided with standardized information regarding the study procedures, potential benefits, possible adverse reactions, and the sensory experiences associated with acupuncture. The information will be presented in a balanced manner to ensure adequate understanding of the intervention without emphasizing potential treatment outcomes. Furthermore, subjective questionnaire data will be evaluated alongside objective ABR measures to provide complementary information regarding clinical changes and associated neurophysiological alterations. The Standard Protocol Items: Recommendations for Interventional Trials (SPIRIT) guidelines will be followed in the development of the protocol (29). Zhejiang Chinese Medical University’s Third Affiliated Hospital will host the study. A total of 72 participants will be included in this study, including 36 patients with chronic tinnitus and 36 healthy controls who matched the patient in age and sex. Healthy controls will be individually matched with tinnitus participants according to sex and age within ±3 years. In addition to demographic matching, we will also compare PTA and audiogram characteristics between the two groups at baseline, as well as before and after treatment within each group. If there are significant intergroup differences in audiogram characteristics, these specific frequencies will be included as covariates in the statistical model used to compare auditory brainstem response (ABR) parameters between groups. The treatment plan includes 10 sessions of acupuncture, which can be completed within 4 weeks and carried out three times a week (usually 2 days apart between each treatment). There are three time points used to evaluate tinnitus-related clinical outcomes and auditory brainstem response (ABR) parameters, namely the baseline period (before the start of treatment), the end of the course (within 1 week after the tenth treatment), and the 8th week after the completion of treatment as follow-up point. The Institutional Ethical Review Board (IRB) of the Third Affiliated Hospital of Zhejiang Chinese Medical University has granted ethical permission for the trial (ZSLL-KY-2025-032-01), which will be conducted in accordance with the Declaration of Helsinki. The Ethics Committee will be notified right away of any amendments to the study design. NCT07522567 is the identification code for this trial’s registration in the Clinical Trials Registry. Table 1 displays the study’s SPIRIT list, while Figure 1 displays the flow diagram.

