
**Table 1 tab1:** SPIRIT schedule of enrollment, interventions, and assessments.

	Study period							
	Enrolment	Allocation	Treatment period				Post-treatment	Follow-up
TIMEPOINT (week)	Week −1(T0)	Week 0	W1	W2	W3	W4	W5 (T1)	W13 (T2: 8-week FU)
Enrolment								
Eligibility screen	X							
Informed consent	X							
Demographic/medical history	X							
Allocation		X						
Interventions								
Acupuncture (10 sessions, 3×/week)			X	X	X	X		
Assessments								
ABR parameters	X						X	
Pure-Tone Threshold testing	X							
Tympanometry & Acoustic reflex testing	X							
DPOAEs	X							
Otoscopic examination	X							
THI	X						X	X
TEQ	X						X	X
Loudness/Annoyance VAS	X						X	X
Adverse events			X	X	X	X	X	

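### Hearing-threshold adjustment depends on significance tests, has no place in the paired baseline ABR test, and leans partly on a post-treatment audiogram that is not scheduled

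*Protocol article*

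**What the plan says.** Three places in the protocol article bear on this.

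- **Design overview (2.1).** Controls are matched on sex and on age within 3 years. The investigators will also "compare PTA and audiogram characteristics between the two groups at baseline, as well as before and after treatment within each group". If the groups differ significantly, "these specific frequencies will be included as covariates in the statistical model used to compare auditory brainstem response (ABR) parameters between groups".
- **Statistical analysis (2.8).** For the baseline case–control comparison, "paired-sample t-tests or Wilcoxon signed-rank tests will be used according to data distribution". The next paragraph sets out a two-way mixed-design ANOVA for longitudinal ABR change, with the group × time interaction as the parameter of interest. The covariate rule stands in that paragraph: "If significant between-group differences in audiometric profiles are detected at baseline or within each group, corresponding frequency-specific hearing thresholds will be included as covariates". All tests are two-sided at 0.05.
- **Table 1.** The row "Pure-Tone Threshold testing" is marked once, at T0. ABR is marked at T0 and T1, and THI at T0, T1 and T2.

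The eligibility criteria give both groups the same hearing limits: PTA below 20 dB HL, no single frequency above 30 dB HL, and normal DPOAEs, tympanometry and acoustic reflexes.

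**The concern.** Hearing threshold is the one confounder that the plan itself singles out beyond age and sex. Three things are fixed badly.

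1. A threshold becomes a covariate only after a significant test. A non-significant test at this sample size does not show balance, and a significant one among several may be chance. Nobody can say before unblinding which model will be fitted.
2. The Design overview promises adjustment of the between-group ABR comparison, but the test named for the baseline comparison has no covariate term and no adjusted alternative is given. That comparison carries Hypothesis 1 and set the case–control sample size.
3. Part of the trigger is a before/after audiogram comparison within each group, and Table 1 provides no second audiogram.

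At stake is whether a baseline wave V difference between patients and controls can be told apart from a difference in hearing thresholds.

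**Working it through.** **The plan's own figure.** This point disputes no figure, but the sample size shows which test is meant. Section 2.9 assumes a paired difference of 0.08 ms with SD 0.14 ms, so d = 0.08/0.14 = 0.571. An exact paired t-test, two-sided 0.05, reaches 80% power with 27 pairs (81.5%). The stated 30 pairs give 85.7%, and 36 give 91.5%. The stated number is therefore on the conservative side; the mismatch is a separate matter. What matters here is that the comparison was planned as a plain paired t-test with no covariate.

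**False triggers.** Section 2.5 lists seven air-conduction frequencies. Take one test per frequency at 0.05 and no true difference:
- Independent tests: 1 − 0.95^7 = 0.302.
- Simulated with 36 pairs and a between-frequency correlation of 0.3, 0.5 and 0.7 (assumed): 0.27, 0.23 and 0.18.

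**Missed gaps at a single frequency.** The documents give no SD for thresholds, so these inputs are assumptions: gap 3 dB, between-subject SD 6 or 8 dB, within-pair correlation r from 0 to 0.3. SD of the paired difference = SD × √(2(1 − r)). Power is from the noncentral t:

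| SD | r | SD of difference | Detected, 36 pairs | Detected, 30 pairs |
|---|---|---|---|---|
| 8 dB | 0 | 11.31 | 34% | 29% |
| 8 dB | 0.3 | 9.47 | 46% | 39% |
| 6 dB | 0 | 8.49 | 54% | 47% |
| 6 dB | 0.3 | 7.10 | 69% | 61% |

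This table holds only for a gap confined to one frequency. If the same 3 dB gap exists at all seven, at least one frequency triggers about 65–92% of the time with SD 8 dB and 83–99% with SD 6 dB (36 pairs, between-frequency correlation 0.3–0.7).

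**Effect on the test.** This was simulated with 36 pairs, one threshold, no true group effect beyond the threshold, a threshold–latency correlation of 0.3–0.5 and a threshold imbalance of 0–0.4 SD of the paired difference (all assumed). Type I error at nominal 0.05:
- Threshold always in a regression of pair differences: 0.048–0.052.
- Threshold included only if significant: 0.043–0.059.
- Never included (the plain paired t-test): 0.048–0.050 when balanced, 0.06–0.22 when the imbalance is 0.2–0.4 SD.

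**Which analysis is exposed.** Suppose a threshold gap adds a constant c to wave V latency in patients. The baseline difference contains c. The change from T0 to T1 does not: (T1 + c) − (T0 + c) = T1 − T0. The group × time interaction is therefore free of it.

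**Schedule.** The within-group clause needs thresholds at two time points. Table 1 supplies T0 only, and neither the audiology section (2.5) nor the outcomes section (2.7) adds another. The between-group part of the trigger can be run from T0 data.

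**The case against.** The strongest reply is that the covariate sentence sits in the mixed-ANOVA paragraph. That model has a group factor and can carry a T0 covariate, and the Design overview does not say that its between-group model is the paired t-test. This stands. A reader might infer that the promised adjustment is impossible anywhere in the plan, and the text does not support that. What remains is that no adjusted form of the baseline comparison is named, and the tests that are named admit none.

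Second, the trigger does little damage to type I error. This also stands: 0.043–0.059 is close to nominal. The larger figures belong to no adjustment at all.

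Third, the shared limits on PTA, single frequencies and DPOAEs already narrow any gap. They do restrict it, but they do not exclude it, since individual frequencies may reach 30 dB HL.

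Fourth, the study calls itself preliminary and hypothesis-generating. That lowers the stakes but does not reconcile the sections.

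A reader might also infer that the plan would adjust for post-treatment thresholds, and so remove part of a treatment effect. The documents do not say so: no such thresholds are scheduled, and the rule does not name the time point of the covariate.

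**Conclusion.** The point holds for three things: a data-chosen adjustment set, a baseline wave V comparison left unadjusted as written, and a within-group trigger without scheduled data.

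The 30% false-trigger figure is an upper value that assumes independent frequencies. The 34–69% detection range rests on an assumed 3 dB gap at one frequency and assumed SDs of 6–8 dB. The exposure concerns the baseline comparison only, not the group × time interaction.

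Two stronger conclusions should be avoided. Large type I error inflation from the trigger is not shown. Nor can the documents support a bias in milliseconds. For illustration only, an assumed slope of 0.005–0.010 ms per dB and a missed 3 dB gap would give 0.015–0.030 ms, or 19–38% of the 0.08 ms target; none of those inputs is in the protocol.

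This should be changed before analysis, but it does not invalidate the design.

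**What to change.** 1. Name a small set of T0 thresholds in advance, for example the ear-averaged 0.5–4 kHz PTA and the 8 kHz threshold, and include them whatever any test shows. The choice of set is the investigators'; what matters is that it is fixed.
2. For the baseline comparison, regress the within-pair wave V difference on the within-pair threshold differences, left uncentred so that the intercept is the adjusted group difference. Alternatively, use a mixed model with a pair effect. Report the unadjusted paired test beside it.
3. Delete the significance trigger from sections 2.1 and 2.8. Audiogram comparisons can stay as description.
4. Reconcile the before/after clause in sections 2.1 and 2.8 with Table 1. Deleting it is cheapest; adding pure-tone testing at T1 in both groups would also resolve it.

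With the clause deleted, this is analysis wording only. The cost is one or two degrees of freedom: with 36 pairs and two covariates, residual degrees of freedom fall from 35 to 33. Adding T1 audiometry instead would cost one more test per participant.

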### Design overview

2.1

This study adopts a hybrid two-part design comprising a matched case–control observational component and a self-controlled interventional component.

In the first component, patients with chronic tinnitus will be compared with age- and sex-matched healthy controls to identify baseline differences in auditory neurophysiological characteristics, including ABR parameters. In the second component, patients with chronic tinnitus will receive a standardized acupuncture intervention and will be followed longitudinally to evaluate changes in subjective tinnitus severity and auditory neurophysiological function. Healthy controls will also undergo two ABR assessment over a comparable time interval to estimate test–retest variability and distinguish treatment-associated changes from normal measurement variability.

There is no sham acupuncture control group in this study. We acknowledge that placebo effects, expectation-related responses, and other non-specific effects associated with acupuncture cannot be completely excluded and may influence the interpretation of treatment-associated changes. To minimize the placebo effect, a strict assessor-blinded design will be adopted. The ABR waveforms will be anonymized and coded before interpretation, with audiologists blinded to both group allocation and time points. Clinical scale interviewers will be blinded to time point, and data analysts will work on a fully coded dataset until the final analysis is locked.

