For the self-controlled interventional component (within the patient group), the sample size was calculated based on anticipated changes in the Tinnitus Handicap Inventory (THI) score, which serves as the primary clinical endpoint for evaluating treatment efficacy. Based on our pilot study and previous clinical observations (35), a mean reduction in THI score of 12.07 points with a standard deviation of 23.28 points after treatment is anticipated. We acknowledge that this standard deviation is relatively large compared to the estimated mean change, which reflects the substantial clinical heterogeneity inherent in chronic tinnitus patients with respect to baseline symptom severity and psychosocial comorbidities. Notably, however, our final target of 36 patients is considerably larger than the minimum required sample size of 24 derived from these pilot estimates. This conservative oversampling strategy enhances the robustness of the study against data overdispersion and potential outliers, and ensures adequate statistical power for detecting the hypothesized treatment effect even with a moderate effect size. For a paired-sample *t*-test (α = 0.05, two-sided; power = 80%), 24 patients are required. To align with the sample size of the case–control component and to account for potential attrition, the final target for the patient group is set at 36 participants.

Thus, a total of 72 people will be included in the study sample: 36 patients with chronic tinnitus and 36 healthy controls who are matched for age and sex. This sample size ensures sufficient statistical power for both the between-group comparisons at baseline and the within-patient longitudinal analysis of treatment effects.

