
### Limitations and future directions

3.1

This study has a number of limitations. Its sample size is comparatively modest because it is a single-center study. Therefore, the results may not be fully extended to a wider range of people with tinnitus. Another limitation is that the intervention group did not include a tinnitus control group receiving sham treatment, making it impossible to compare the effects of true acupuncture and sham acupuncture on patients with tinnitus. This is particularly worthy of attention, because the 2024 VA/DOD guidelines found insufficient evidence of acupuncture, and thus emphasized the need to carry out good controlled trials. While the self-controlled design allows each patient to serve as their own control and reduces between-subject variability, it cannot fully distinguish specific acupuncture effects from placebo effects, regression to the mean, or non-specific treatment effects. Although the inclusion of a healthy control group with repeated ABR measurements helps quantify normal test–retest variability, it does not replace a parallel sham-controlled arm. Therefore, our findings should be interpreted as preliminary and hypothesis-generating. Future adequately powered, sham-controlled randomized trials are needed to definitively establish the efficacy of acupuncture for chronic tinnitus. Third, the ABR protocol in this study uses broadband click stimuli rather than frequency-specific tone bursts. While this choice ensures clinical standardization and comparability with previous literature, it may reduce the sensitivity to detect frequency-specific cochlear synaptopathic changes that have been suggested to underlie some forms of tinnitus (51). Future studies incorporating multiple frequency-specific stimuli (e.g., 1, 2, and 4 kHz tone bursts) would provide a more comprehensive assessment of the relationship between acupuncture, ABR parameters, and tinnitus pathophysiology. Fourth, this study employs an assessor-blinded design rather than a double-blind design. Due to the nature of the acupuncture intervention, neither patients nor acupuncturists can be blinded to treatment allocation, which may introduce performance bias and expectation effects. To mitigate this, we have implemented several measures which have been motioned in the Design overview section. Nonetheless, we acknowledge that the lack of patient blinding remains a limitation. Fifth, treatment adherence is currently assessed primarily by session attendance, which does not fully capture treatment fidelity. To strengthen this aspect, all acupuncturists will follow a detailed Standard Operating Procedure (SOP) manual, needle manipulation parameters (angle, frequency, and duration) will be recorded for each session, and the De Qi sensation will be assessed using the C-MASS scale after each session. These additional measures will allow us to characterize the consistency of treatment delivery beyond simple attendance records. In addition, although ABR measurement is valuable for evaluating brainstem function, it cannot capture changes in the cortical level, which may also affect the perception of tinnitus. Lastly, this study did not set up a long-term follow-up beyond the treatment period, so it is impossible to evaluate whether the observed effect is persistent. And the 8-week follow-up assessment was conducted by telephone, which may introduce recall bias and reduce the accuracy of symptom evaluation compared with face-to-face assessment.

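### The primary THI outcome spans two changes and is judged by one three-visit ANOVA, which neither isolates the pre-post change the trial is sized on nor keeps every patient who has it

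*Protocol article*

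**What the plan says.** Section 2.7.1.1 defines the primary clinical outcome as "the change in the Tinnitus Handicap Inventory (THI) score from baseline to post-treatment and follow-up". That is two changes, and neither is named as the deciding one.

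Section 2.8 analyses THI, TEQ and VAS in the tinnitus patients "using one-way repeated-measures ANOVA across baseline, post-treatment, and 8-week follow-up". It names no primary contrast, post-hoc comparison or multiplicity rule for THI. The Bonferroni step there belongs to the ABR group-by-time interaction, and the false discovery rate step to secondary ABR parameters. On missing data it says: "Linear mixed-effects models or multiple imputation methods will be considered for sensitivity analyses if substantial missing longitudinal data occur".

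Section 2.9 sizes the interventional component on one paired comparison: "a mean reduction in THI score of 12.07 points with a standard deviation of 23.28 points after treatment is anticipated", leading to "α = 0.05, two-sided; power = 80%), 24 patients are required". The target is 36. The section calls this the pre-post comparison within patients and says that sizing is anchored to a single contrast.

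Section 3.1 states that "the 8-week follow-up assessment was conducted by telephone" and concedes that this may be less accurate than assessment in person. Sections 2.1 and 2.7 date T2 differently: eight weeks after treatment ends (Table 1 has week 13) and eight weeks after treatment begins.

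**The concern.** Outcome, test and sample size are all stated, and they do not address the same quantity. The sample size concerns T0 to T1. The test asks whether the three visit means differ anywhere, with 2 numerator degrees of freedom. A significant result could come from T1, from T2 or from both, and the plan does not say which comparison then supports the efficacy claim.

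Two features of T2 add to this. First, classical repeated-measures ANOVA needs all three visits, so a missed follow-up call removes a patient whose T0-T1 change was observed. Second, T2 has a different mode of collection, so any effect of mode on THI is mixed with the effect of time at that visit and enters the primary test. At stake are the meaning of the headline p-value and some avoidable loss of power.

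**Working it through.** **Inputs.** From section 2.9: mean change 12.07, SD of change 23.28, two-sided α 0.05, power 80%, stated requirement 24, target 36, attrition 20%. Assumed, because the article gives no figures: compound symmetry, an SD of 23.28 for every pairwise change including those involving T2, and the split of attrition between visits.

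**1. The plan's own figure.** d = 12.07/23.28 = 0.518. For a two-sided paired t-test, power comes from the noncentral t with n − 1 degrees of freedom and noncentrality d√n.

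| n | d√n | Power |
|---|---|---|
| 24 | 2.540 | 68.2% |
| 29 | 2.792 | 76.9% |
| 31 | 2.887 | 79.8% |
| 32 | 2.933 | 81.1% |
| 36 | 3.111 | 85.6% |

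The requirement is therefore 32, not 24. The normal approximation gives (1.960 + 0.842)²/0.518² = 29.2, so 30. A one-sided calculation gives 25 (t) or 23 (normal), close to the stated figure. The reserve of 36 over the requirement is thus smaller than section 2.9 claims.

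**2. What the omnibus F responds to.** Under compound symmetry the error variance is 23.28²/2 = 270.98. The noncentrality is λ = n·Σ(μⱼ − μ̄)²/270.98, with 2 and 2(n − 1) degrees of freedom.

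No change at T1, fall at T2 only:
- Fall of 12.07: Σ = (2/3)·12.07² = 97.12. At n=36, λ = 12.90 and the test rejects in 89%. At n=29, λ = 10.39 and it rejects in 81%.
- Fall of 6: Σ = (2/3)·6² = 24. At n=36, λ = 3.19 and it rejects in 33%. At n=29, λ = 2.57 and it rejects in 27%.

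In all four cases the T0-T1 paired test rejects at its nominal 5%.

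**3. Power when the planned T0-T1 effect is present (n=36).**

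| T2 relative to T1 | Σ | λ | Omnibus F | T0-T1 paired t |
|---|---|---|---|---|
| Benefit fully kept | 97.12 | 12.90 | 89% | 86% |
| Half kept | 72.84 | 9.68 | 78% | 86% |
| Fully lost | 97.12 | 12.90 | 89% | 86% |

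**4. Patients dropped for a missing T2.**
- 10% lost before T1 and a further 10% after: 36 × 0.9 = 32.4, so 32 have T0 and T1; 32.4 × 0.9 = 29.2, so 29 have all three visits. Power for the T0-T1 contrast is 81% with 32 and 77% with 29.
- All 20% lost after T1: 36 have T0 and T1, and 36 × 0.8 = 28.8, so about 29, have all three. Power is 86% against 77%. This is the extreme split.
- All 20% lost before T1: nothing is lost by using the ANOVA, because those patients have no T0-T1 change under any method.

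**The case against.** The strongest reply is that T2 is a declared part of the primary outcome, so a three-visit test matches section 2.7.1.1. That stands. A reader might infer from step 2 that a result driven by T2 is a false positive, or that the test fails Hypothesis 2. The article supports neither: Hypothesis 2 speaks of improvement following ten sessions and does not confine THI to T1. The mismatch is with the contrast that was sized, and with the absence of a rule saying which change decides.

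A reader might also infer that the omnibus test is weaker throughout. Step 3 shows that it is stronger when the benefit is fully kept or fully lost. The scenario with an effect at T2 alone shows what the test can respond to; nothing in the article makes it likely.

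The article does not say that incomplete patients are excluded. This follows from the method, and the approaches that keep such patients are only to be considered for sensitivity analyses. Section 2.8 does contain a paired baseline to post-treatment test, but it stands in the ABR paragraph, is additional, and is not named as the primary THI test. Post-hoc detail can be left to an analysis plan; a primary outcome, test and sample size that disagree in the same document are a different matter.

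On the telephone visit, the limitation is disclosed, though not its entry into the primary test. Two further inferences go too far. One is that the VAS cannot be collected by telephone: the article specifies only 0–10 scores, and VAS is secondary. The other is that the statement "Clinical scale interviewers will be blinded to time point" is necessarily defeated: a call may reveal the visit, but the article does not describe how blinding is arranged.

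**Conclusion.** The point holds. The primary THI outcome names two changes, the test isolates neither, and the sample size covers one. The main consequence is interpretive: a significant F does not establish the T0-T1 improvement for which the trial was sized, and under the stated assumptions it occurs in 27% to 89% of trials in which only T2 moves (by 6 or 12.07 points, n from 29 to 36).

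The power cost is secondary and uncertain. It is about four percentage points with an even split of losses, nine if all attrition falls after T1, and none if all falls before. A reader might take 29 instead of 36 as the expected loss, but the article gives only an overall attrition rate. The margin matters more because the stated inputs require 32 patients with the change observed, not 24. Any mode effect at T2 is confounded with time, and its size is unknown.

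**What to change.** - In sections 2.7.1.1 and 2.8, name the T0-T1 THI change as the single primary clinical contrast, matching section 2.9.
- Estimate it from a linear mixed model with visit as a categorical factor, using all available THI data, as the main analysis. Patients who miss only T2 then still contribute.
- Make T0-T2 a secondary contrast from the same model, to be interpreted with the telephone mode in mind.
- Reconcile the two definitions of T2 in sections 2.1 (with Table 1) and 2.7.

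This is a change of wording and of analysis; it needs no new data, and the mixed model is already listed as an option. The price is that T2 loses its primary status, and the mixed model relies on missing values being explained by the data observed.
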